### Primary Outcomes: FC Changes in the DMN

We hypothesize that active cTBS will disrupt the within-network and between-network connectivity of the DMN. This hypothesis will be assessed from a 10-minute resting-state FC scan and analyzed using standard procedures in the CONN (v17f or higher). Standard pipelines for preprocessing will be used. Within-network connectivity will be determined by first conducting an independent components analysis of the intrinsic activation patterns across the brain. Twenty independent components will be extracted. Mean activation clusters from each component will be examined for intercorrelation to determine within-network connectivity. Additionally, between-network, region-to-region, and seed-to-voxel analyses will be conducted to compare changes in FC between the 2 stimulation conditions.

### Analysis Plan

#### FC Changes to the DMN

First-level whole brain connectivity analyses will be undertaken in CONN for each subject at each of the 4 sessions (ie, active prestimulation, active poststimulation, sham prestimulation, and sham poststimulation). This will result in an FC map for each participant at each session, indicating the magnitude and direction of intrinsic correlation between each seed region (eg, lateral parietal cortex of the DMN) and all other voxels in the brain. For our primary analysis, we will estimate the effects of active cTBS on FC within the DMN using multimodal neuroimaging data including resting state FC. Raw NifTI images will be preprocessed using standard functional preprocessing pipelines in CONN [46].

The first-level connectivity maps will be combined in subsequent second-level analyses in CONN to explore the effects of cTBS stimulation on brain connectivity to include (1) independent components analysis, (2) seed-to-voxel analyses, and (3) region of interest to region of interest analyses [44]. Statistically significant differences in FC of the DMN between sham and active conditions will be the minimal important change to confirm the primary hypothesis. Next, PSG parameters measuring sleep stage duration and onsets, arousals, and awakenings will be added as covariates of FC change from before to after stimulation, comparing sham and active cTBS conditions.

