### Study Design and Randomization

This phase 1 clinical trial (ClinicalTrials.gov NCT04953559) will be conducted with a randomized, double-blind, sham-controlled, counterbalanced, crossover design. Participants serve as their own controls as they undergo 2 identical study sessions separated by at least 5 days (ie, washout period). Participants and study personnel who interact with the participants will be blind to the specific condition (active cTBS vs sham) the participant receives during each study visit. Using a prespecified, equally balanced, block randomization procedure, participants will be assigned to the order in which they receive active cTBS and sham stimulation conditions. The randomization list will be generated by a computer random number generator, with the constraint that half of the participants of each biological sex will receive sham first and half will receive the active cTBS first. This design will allow us to examine the intraindividual effects of the active cTBS and establish the superiority of active cTBS compared with sham stimulation in improving PSG sleep outcomes.

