#### Intervention: cTBS Versus Sham

Following the first MRI scan, participants exited the scanner and underwent either cTBS stimulation or sham stimulation according to their preassigned double-blinded condition. The stimulator was preprogrammed prior to the start of the session and the participants and technicians that administered the stimulation procedure were blind to the administered condition. Each individual was expected to have a different sensitivity to the magnetic fields generated by the stimulation coil, and the stimulation intensity was adjusted based on each individual’s resting motor threshold (RMT). The real-time, motor-evoked potential of muscle contraction is provided to ensure consistent force production. Once the RMT was identified, the stimulation intensity for TBS was set to 70% of each participant’s RMT.

For primary rTMS stimulation, we located a predetermined node in the inferior parietal lobe, localized by coregistering the participant’s head, structural T1-weighted MRI image, and TMS coil in the same space using a TMS 3D Neuronavigation System. Once coregistration was complete, the Neuronavigation system provided real-time feedback on the TMS coil location and recorded the coil position and orientation relative to the head. The cTBS was applied using a figure-of-8 coil with an active cooling system connected to the MagPro magnetic stimulator (MagVenture Cool-B65). The same coil has 2 sides, 1 designed for active TMS stimulation, and the other is equipped with a magnetic shield that effectively blocks any stimulation and is used for the sham condition. The rTMS setup is shown in Figure 3.

For this project, we selected an easily accessible node of the DMN located on the left lateral parietal (LLP) cortex. The exact spatial location for stimulation is based on the Yeo et al [45] probability atlas. We downloaded this atlas into the Mango 4.1 visualization program (and identified the centroid of the LLP node of the DMN at the MNI coordinates of x (–48), y (–61.5), and z (32.5). These coordinates are converted into the same stereotaxic space as the participant’s brain to allow precision localization of the LLP node as the target for stimulation. Once this site was localized for the participants, a 40-second cTBS stimulation train (600 stimuli/session) or identically matched sham stimulation was administered using a MagVenture MagPro X100 stimulator (MagVenture Inc) connected with a figure-of-8 magnetic coil with active cooling.

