#### PSG Recording

Participants slept undisturbed in a light- and temperature-controlled private bedroom while continuously monitored by a trained technician with a Nihon Kohden JE-921 PSG recording system using standard 10-20 electrode placement. Data from PSG were scored using Polysmith software according to the standard Rechtschaffen and Kales approach by a trained and certified sleep technician who was blind to the participant’s condition and status. The primary outcome metrics include sleep onset latency (SOL), latency to N1, N2, N3, and REM, total sleep time (TST), sleep efficiency (SE), wake after sleep onset (WASO), and number of awakenings and arousals, as well as time and percentage of time spent in each sleep stage.

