#### Data Management

All collected data were deidentified and stored within HIPAA-compliant, password-protected servers immediately after collection. Study data were only accessible to IRB-approved study staff. All data were checked and double-entered by study personnel no more than 1 week after data collection. Data quality checks were conducted every quarter by staff members for additional data assurance. Any data collected after participants’ consent were included in the study database for both compliant and noncompliant participants. However, following a per-protocol analysis, we are only using data from participants who fully completed the study due to within-subjects analysis.

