## Results

Our study was funded in September 2020 by the Department of Defense (W81XWH2010173). We completed the enrollment of our target population of 20 participants in October 2022. As of July 2023, we will initiate extensive neuroimaging data analysis and anticipate that the full results of the study will be published by 2024.

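### Blinding is stated for the PSG scorer but not for those who analyse the FC scans, while the DMN definition stays open and any significant FC difference confirms the primary hypothesis

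*Protocol article*

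**What the plan says.** All places are in the protocol article.

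- **Who is blind.** *Study Design and Randomization*: "Participants and study personnel who interact with the participants will be blind to the specific condition". *Intervention: cTBS Versus Sham* adds that "the participants and technicians that administered the stimulation procedure were blind to the administered condition". *PSG Recording* has the sleep data scored "by a trained and certified sleep technician who was blind to" condition and status.
- **Who is not mentioned.** No section states blinding for those who preprocess the scans, identify DMN components or choose seeds. The only general rule on access, in *Data Management*, is that "Study data were only accessible to IRB-approved study staff".
- **What is open in the FC outcome.** *Primary Outcomes: FC Changes in the DMN* fixes a number: "Twenty independent components will be extracted". It does not say which components count as the DMN or by what rule, and clusters come from each component's output. *Analysis Plan, FC Changes to the DMN* gives one seed region as an example.
- **How the FC analysis is described.** The same section describes first-level maps "at each of the 4 sessions (ie, active prestimulation, active poststimulation, sham prestimulation, and sham poststimulation". It then names three second-level families: independent components, seed-to-voxel and region-to-region.
- **When FC success is declared.** A statistically significant active-versus-sham difference in DMN connectivity confirms the primary hypothesis. No single contrast is named.
- **Timing.** The *Results* section says "As of July 2023, we will initiate extensive neuroimaging data analysis". The abstract says that neuroimaging processing and analysis are already in progress.

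**The concern.** Table 1 places FC and PSG side by side as primary outcomes. The person whose judgement shapes the PSG result is blinded by name. The people whose judgement shapes the FC result are not, and the general blinding statement, limited to staff who interact with participants, does not reach an analyst who never meets one.

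This matters because the FC outcome involves judgement. Someone must decide which of twenty components are the DMN, which clusters are kept and which seeds are run. If the active-versus-sham contrast can be seen while those decisions are made, they can drift, without any bad intent, toward the definition that shows a difference. The FC estimate would then be biased toward an effect and its false-positive rate raised. The article's own rationale credits blinding of personnel with reducing the influence of expectations, and that reasoning applies equally here.

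**Working it through.** **1. Blinding by role**

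| Role | Blinding stated? | Section |
|---|---|---|
| Participants and staff who meet them | Yes | Study Design and Randomization |
| Stimulation technicians | Yes | Intervention: cTBS Versus Sham |
| PSG scorer | Yes | PSG Recording |
| FC preprocessing and analysis staff | Not stated | Data Management gives an access rule only |

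**2. What is fixed and what is open in the FC outcome**

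- Fixed: twenty components; standard CONN pipelines; an atlas coordinate for the stimulation target.
- Open: the DMN component(s) and the rule for picking them; the clusters; the seed list beyond one example; which of the three second-level families carries the primary hypothesis. The stimulation coordinate is not declared to be the only FC seed.

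**3. What the session names show.** The four names are two conditions crossed with two time points. A masked analyst could run the same four sessions under codes. First-level maps are made per subject and session, so the label does not change the map. The names therefore do not establish an open allocation code.

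**4. Size of the risk (illustration only).** The article gives no figure to reproduce on this point. Assumptions: two-sided 0.05 per test (the article states no alpha), *k* candidate DMN definitions, and the most favourable one kept.

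Independent definitions: false-positive rate = 1 − 0.95^*k*.

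- *k* = 2: 1 − 0.9025 = 9.8%
- *k* = 3: 1 − 0.8574 = 14.3%
- *k* = 4: 1 − 0.8145 = 18.5%

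For equally correlated definitions with correlation *r*, the rate is the probability that at least one of *k* standard normal statistics exceeds 1.96 in absolute value:

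1 − ∫ φ(u) [Φ((1.96 − u√r)/√(1−r)) − Φ((−1.96 − u√r)/√(1−r))]^*k* du

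| *k* | *r* = 0 | *r* = 0.5 | *r* = 0.8 |
|---|---|---|---|
| 2 | 9.8% | 9.1% | 7.8% |
| 3 | 14.3% | 12.5% | 9.8% |
| 4 | 18.5% | 15.6% | 11.4% |

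**5. What masking would and would not restore.** Suppose one DMN definition is locked, but a significant result in any of the three second-level families still counts. At 0.05 each, the rate is 14.3% if the families are independent. Simulated paired t tests with n = 20 give 13.4%, 12.4% and 11.2% at correlations of 0.3, 0.5 and 0.7. The rate returns to 5% only if one primary contrast is fixed as well.

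**The case against.** The strongest reply is that nothing here shows an unblinded analysis. A reader might infer from the session names that each scan is handed to the analyst labelled active or sham. The article does not support that: any plan, including one with masked analysts, would describe the design cells this way. This objection stands in full.

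Second, a condensed article commonly leaves seed lists, component rules and analyst masking to the full protocol or analysis plan. That also stands, so the point does not rest on a missing seed list. It rests on what the article does set out: blinding given role by role that reaches the assessor of one primary outcome and not the other, together with an open outcome definition and a success rule met by a significant DMN difference.

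Third, the percentages measure selection among open definitions, not the effect of visible labels. An analyst with a constant A/B code could still keep the largest difference. This is correct. It is why the figures are an illustration only and why the codes must be randomised within each participant.

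Fourth, a reader of the *Results* section alone might conclude that imaging analysis has yet to begin and masking can be applied throughout. The abstract says processing and analysis are under way, so part of the protection may already be lost. It would also be too strong to say the harm could not then be repaired: reporting all candidate definitions with a multiplicity adjustment addresses it.

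**Conclusion.** The point holds in a limited form. The stated blind does not extend to those who process and analyse the FC scans, and the article leaves the DMN component(s), clusters and seeds open while a significant FC difference confirms the primary hypothesis. The plan as written permits DMN choices with allocation visible; it does not show that any were made that way. If the imaging analysts were already masked, one sentence saying so answers the masking part.

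Under the stated assumptions (two-sided 0.05 per test, two to four candidate definitions, correlations from 0.8 down to 0, best one kept), the false-positive rate would be about 8% to 18.5%. The true rate cannot be derived from the article. Masking alone does not bring it to 5%; a single primary contrast across the three analysis families is also needed. This should be changed because the protection is cheap, but it is not evidence that the FC result is already compromised.

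**What to change.** 1. Release scans to the imaging analysts under session codes randomised separately for each participant, so that no group contrast between active and sham can be formed. Someone outside the FC analysis holds the key.
2. On coded data, complete preprocessing, any scan exclusions and the independent components analysis. Choose the DMN component(s), clusters, seeds and one primary FC contrast. Date-stamp and lock these choices.
3. Unmask only for the second-level active-versus-sham contrast.
4. State in the plan who in the imaging team is masked, and until when.
5. If work on labelled scans has already been done, disclose it and report the contrast for every candidate DMN definition, with a multiplicity adjustment across them.

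The cost is a file-renaming script, a dated lock note and a short delay before the contrast can be viewed. No new study procedure is needed.

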**Results:**

Our study was funded in September 2020 by the Department of Defense (W81XWH2010173). We completed the enrollment of our target study population in the October 2022 and are currently working on neuroimaging processing and analysis. We aim to publish the results of our study by 2024. Primary neuroimaging outcome measures will be tested using independent components analysis, seed-to-voxel analyses, and region of interest to region of interest analyses. A repeated measures analysis of covariance (ANCOVA) will be used to assess the effects of active and sham stimulation on sleep variables. Additionally, we will correlate changes in functional connectivity to polysomnography-graded sleep.

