The proposed protocol aims to bridge the gap between cognitive and neuromodulatory interventions to facilitate sleep onset and longer maintenance by temporarily inhibiting the brain FC that is associated with cortical hyperarousal and presleep ruminative cognitions. Our proposed approach will involve using rTMS prior to bedtime to briefly disrupt the strength of FC among cortical regions of the DMN. As we propose to inhibit connectivity within the DMN, we will use continuous theta burst stimulation (cTBS), which induces long-term depression of cortical neural firing following a sustained stimulation period of 40 seconds [40]. Thus, we hypothesize that the application of cTBS to an easily accessible node of the DMN will suppress the local neural activity of that node and propagate inhibition throughout the DMN, thereby reducing ruminative thinking and worry prior to sleep onset. Decreased DMN connectivity is expected to improve sleep quality and quantity. An increase in slow-wave and rapid eye movement sleep stages has been proposed as mechanisms of rTMS in increasing restorative sleep in individuals with insomnia, so polysomnography (PSG) parameters are the primary outcome measures in the outlined protocol [41]. This phase 1 clinical trial will be the first study to investigate the effects of cTBS targeted to the left inferior parietal node of the DMN on objectively measured sleep outcomes.

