### Research Aims and Hypotheses

This study aims to explore the effects of cTBS on (1) the activation and connectivity of the DMN and (2) sleep outcomes. We hypothesize that modulating the DMN by stimulating a targeted region of the left inferior parietal lobule with a single cTBS administration will decrease FC within the DMN and thereby improve sleep parameters (ie, PSG) relative to an identical sham administration.

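### The rule for confirming the primary connectivity hypothesis has no direction and no deciding analysis, although the stated hypothesis is a decrease in connectivity within the default mode network

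*Protocol article*

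**What the plan says.** The hypothesis has a sign. Under Research Aims and Hypotheses, stimulating the left inferior parietal lobule "will decrease FC within the DMN and thereby improve sleep parameters", relative to sham. The Introduction (Overview) makes that sign the mechanism: "Decreased DMN connectivity is expected to improve sleep quality and quantity".

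Under Primary Outcomes: FC Changes in the DMN the sign is gone and the scope is wider: "We hypothesize that active cTBS will disrupt the within-network and between-network connectivity of the DMN".

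Under Analysis Plan, FC Changes to the DMN, three second-level analyses are listed. The Abstract (Results) ties all three to the primary outcome: "Primary neuroimaging outcome measures will be tested using independent components analysis, seed-to-voxel analyses, and region of interest to region of interest analyses". The same Analysis Plan section then fixes the decision rule: "Statistically significant differences in FC of the DMN between sham and active conditions will be the minimal important change to confirm the primary hypothesis".

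That section also says that the primary analysis estimates the effect on FC within the DMN, and it names the lateral parietal cortex only as an example of a seed. The PSG Analysis section uses the same significance-as-minimal-important-change wording for sleep.

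**The concern.** The predicted result is a decrease, but the rule asks only for a difference. The sign matters here because the rationale is that people with insomnia have raised DMN connectivity and that lowering it should help sleep. An increase would speak against the mechanism, yet the rule as worded does not exclude it.

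The rule also does not say whether one, a particular one, or all of the three analyses must be significant. If any one suffices, there are three chances to confirm.

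Finally, the rule treats a p-value as a minimal important change. Significance depends on sample size and variability as well as on effect, so it cannot stand in for a size that matters. At stake is whether a reported confirmation of the primary hypothesis means what a reader will take it to mean.

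**Working it through.** **The wording, section by section**

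| Section | Direction | Scope |
|---|---|---|
| Introduction (Overview) | decrease | DMN connectivity |
| Research Aims and Hypotheses | decrease | within the DMN |
| Primary Outcomes | none (disrupt) | within- and between-network |
| Analysis Plan, decision rule | none (differences) | FC of the DMN, after three analyses |

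The first two rows agree. The last two drop the sign, and the third also widens the target.

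**Illustrating the rule as written**

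The article gives no error rate to reproduce. Inputs:
- From the document: three analyses and 20 participants, each receiving active and sham.
- Assumed, because not stated: 0.05 two-sided per analysis, one test in each, no correction across the three, and no true effect.

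At least one of three significant, if independent: 1 − 0.95³ = 0.143.

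At least one significant increase, if independent: each analysis has 0.025 in the upper tail, so 1 − 0.975³ = 0.073.

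All three analyses use the same scans, so they will be correlated. Simulating 400,000 draws of three equally correlated standard normal statistics, with cut-off 1.96, gives:

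| Correlation | Any significant difference | Any significant increase |
|---|---|---|
| 0 | 14.3% | 7.3% |
| 0.3 | 13.6% | 6.8% |
| 0.5 | 12.6% | 6.3% |
| 0.7 | 10.9% | 5.5% |
| 0.9 | 8.3% | 4.1% |

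**The same quantities under a signed, single-contrast rule**

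One named contrast, tested two-sided at 0.05 and confirmed only by a decrease: the null probability of confirmation is 0.05 / 2 = 0.025, and of confirmation by an increase it is 0.

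If all three analyses stay confirmatory with Bonferroni, each is tested at 0.05 / 3 = 0.0167. The chance of any significant result is 1 − (1 − 0.0167)³ = 0.049 if independent. Requiring a decrease brings it to at most 3 × 0.0167 / 2 = 0.025.

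**Price of the two options at N = 20** (paired t, 19 degrees of freedom, 80% power): the detectable standardised paired effect is 0.66 at 0.05 two-sided and 0.78 at 0.0167 two-sided.

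**The case against.** The best defence is that the rule confirms the primary hypothesis, and that hypothesis is elsewhere a decrease, so a sensible reader would not count an increase. That is fair as to intent. A reader might infer that the investigators mean to accept an increase; the document does not say so. But the outcomes section restates the hypothesis without a sign, so the rule cannot simply borrow one.

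A second defence is that components, regions, thresholds and multiplicity belong in an analysis plan that is not shown. This stands: their absence from an article is no fault, and within-analysis correction may well be planned. The point rests on the decision rule that the article does print, which does not match its own hypothesis.

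A third is that this is a pilot of 20 people and that the second-level work is described as exploring effects. That lowers the stakes, but the same section speaks of confirming the primary hypothesis, and Study Design and Randomization speaks of establishing superiority on sleep outcomes.

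Two stronger readings fail:
- A reader might count within- and between-network tests by three methods as six looks, giving 1 − 0.95⁶ = 26.5%. The Analysis Plan centres the primary analysis on FC within the DMN, so six equally confirmatory looks is not what it describes.
- A reader might say that the hypothesis cannot fail. It can: it fails if nothing is significant.

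Two-sided testing is not a fault either. What is missing is the sign in the rule for claiming confirmation.

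**Conclusion.** The concern holds as an inconsistency between a signed hypothesis and an unsigned decision rule that names no deciding analysis. That an increase, or any one of the three analyses, would suffice is the literal reading of the rule rather than the document's own words.

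Under the stated assumptions, the chance of at least one false positive is 8.3% to 14.3% for correlations from 0.9 down to 0, and the chance of at least one significant increase is 4.1% to 7.3%. These figures show what the rule permits; they are not the trial's error rate, since alpha and any correction across analyses are unknown. The misuse of significance as a minimal important change needs no assumption: the text states it.

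**What to change.** Reconcile Research Aims and Hypotheses, Primary Outcomes, and the Analysis Plan so that they state one hypothesis with one direction and one scope. Then:

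1. Name one primary contrast: (post minus pre, active) minus (post minus pre, sham), in mean FC among the core DMN nodes listed in the Introduction. This fits the Power Analyses section, which is already framed around mean change in DMN connectivity.
2. Test it two-sided, and state that only a significant decrease confirms the hypothesis.
3. Report the estimate with its 95% CI and drop the minimal-important-change label, here and in PSG Analysis. If a minimal important size is wanted, set it separately from significance.
4. Make the other FC analyses supportive, or adjust across the three.

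No new data are needed. The cost is that the other maps lose confirmatory status or, if all three are kept with Bonferroni, that the detectable effect rises from 0.66 to 0.78. The change is not purely editorial: the Results section has imaging analysis starting in July 2023, and the Abstract says that processing and analysis are already under way. The report should therefore disclose when the primary contrast was chosen relative to unblinded results.

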**Covariates**							
	Demographics	✓					
	Anxiety (STAI-S^f^ and STAI-T^g^)	✓				✓	
	Depression (BDI-II^h^)	✓				✓	
	Sleep preoccupation (SPS^i^ and GCTI^j^)	✓				✓^k^	
	Caffeine consumption questionnaire	✓					
	Intelligence (WASI-II^l^)	✓					
	Actigraphy (Phillips Actiwatch)			✓			
	Sleep quality (Sleep diaries)			✓			

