### Power Analyses

During the study design, we conducted a power analysis to determine the sample size necessary to compare mean changes in DMN connectivity before and after cTBS using a within-subjects ANOVA approach. From prior cited work on transcranial magnetic stimulation (TMS) and FC, a total sample of 20 was found to have sufficient power to answer the research questions to include analysis of 2 groups (within-subject active and sham), 2 repeated measurements (before and after TMS), and a correlation between the change in DMN activation and sleep outcome metrics [42,43].

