#### PSG Analysis

We will assess the effects of active cTBS on sleep and whether participants demonstrated greater sleep quality during their active cTBS session compared with their sham stimulation session. Analyses will be conducted on sleep variables including total sleep time; N1 latency; N2 latency; N3 latency; REM latency; SOL; persistent SOL; SE; WASO; total number of awakenings; spontaneous arousals; wake duration; and stage duration for N1, N2, N3, and REM. Analyses will include repeated measures ANOVA controlling for covariates. Statistically significant difference between sham and active conditions will be the minimal important change to confirm this hypothesis.

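### The follow-on FC step, read literally, adjusts the active-sham contrast for later sleep, and the sleep ANCOVA leaves room for person-level covariates that cannot help and, if uncentred, can hide the effect

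*Protocol article*

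**What the plan says.** **FC model.** The Analysis Plan (FC Changes to the DMN) first sets the confirmation rule: "Statistically significant differences in FC of the DMN between sham and active conditions will be the minimal important change to confirm the primary hypothesis". No covariate is named for that test. The following sentence, which opens with the word Next, says that PSG parameters on sleep stages, arousals and awakenings "will be added as covariates of FC change from before to after stimulation, comparing sham and active cTBS conditions". Elsewhere the same link is described as a correlation: the Abstract (Results) says so, and Power Analyses plans for "a correlation between the change in DMN activation and sleep outcome metrics".

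**Sleep model.** PSG Analysis states: "Analyses will include repeated measures ANOVA controlling for covariates". A significant active-sham difference then confirms the sleep hypothesis. The Abstract puts it as: "A repeated measures analysis of covariance (ANCOVA) will be used to assess the effects of active and sham stimulation on sleep variables". Neither place names the covariates. Table 1 has a block headed Covariates. Demographics, the caffeine questionnaire, WASI-II and the Sleep Preoccupation Scale are ticked at visit 1 only. Anxiety, BDI-II and GCTI are also ticked at the overnight visits, and actigraphy and diaries are collected at home.

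**The concern.** Two separate problems arise.

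1. The Figure 2 caption puts stimulation between 1900 and 2000, then the second scan, then lights out at 2300. Research Aims and Hypotheses expects FC to fall and sleep to improve as a result. PSG is therefore downstream of both treatment and the FC measurement, and Table 1 lists it as a primary outcome. An active-sham FC contrast adjusted for it no longer estimates the effect of stimulation on FC. It can shrink a real effect, or produce an apparent one where only sleep responded.

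2. In a crossover, a value that is constant within a person cancels from the active-sham difference, so adjustment removes no confounding. Standard repeated-measures ANCOVA enters such a covariate with a condition interaction. If it is not centred, the condition main effect is the effect at covariate zero, for example at age 0 or IQ 0. That test answers no question the trial asks, and it carries the confirmation rule for sleep.

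**Working it through.** **The plan's own figure.** Power Analyses reports that "a total sample of 20 was found to have sufficient power to answer the research questions" and describes a test to "compare mean changes in DMN connectivity before and after cTBS using a within-subjects ANOVA approach". It gives no alpha, power, effect size or SD, so N = 20 cannot be reproduced. I assume two-sided 0.05 and a standardised paired effect dz. With n = 20 and 19 df, noncentral-t power is 0.25 at dz 0.3, 0.56 at 0.5, 0.80 at 0.66 and 0.92 at 0.8. I use dz = 0.66 below because it gives 80%; it is not a figure from the article.

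**A. FC contrast adjusted for sleep.** Work on within-person active-minus-sham differences, each with SD 1 and oriented so that positive is the hypothesised direction. Let d be the FC effect, s the sleep effect and ρ the correlation of the two differences. Regressing the FC difference on the sleep difference gives intercept d − ρs.

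| ρ | Adjusted contrast, d = s = 0.66 | Simulated power | Adjusted contrast, d = 0, s = 0.66 | False rejection |
|---|---|---|---|---|
| 0.3 | 0.66 − 0.198 = 0.46 | 0.39 | −0.20 | 0.10 |
| 0.5 | 0.66 − 0.33 = 0.33 | 0.26 | −0.33 | 0.25 |
| 0.7 | 0.66 − 0.462 = 0.20 | 0.16 | −0.46 | 0.60 |

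The size depends on s. If the sleep effect is only ρ times the FC effect, the contrast becomes d(1 − ρ²): at ρ = 0.5, 0.66 × 0.75 = 0.495, a loss of 25% instead of 50%, with power about 0.61. If the sleep difference is centred, so that the model describes association only, the mean FC contrast stays at 0.66.

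Degrees of freedom are also short. PSG Analysis lists 16 sleep variables; entering all of them jointly would leave 19 − 16 = 3. The FC section describes a narrower set, so this is the extreme case.

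**B. Person-level covariates in the sleep model.** The condition effect is the intercept of the active-sham difference on the covariates.

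*Centred.* The estimate is unchanged and each covariate costs one df. At dz 0.66, power is 0.799 with none, 0.797 with one, 0.794 with two and 0.784 with five.

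*Uncentred.* For one covariate, the SE is multiplied by √(1 + (mean/SD)² × n/(n − 1)).

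- IQ, assumed mean 100 and SD 15: √(1 + 44.44 × 20/19) = √47.78 = 6.91. The noncentrality falls from 0.66 × √20 = 2.95 to 2.95/6.91 = 0.43, and power on 18 df is about 0.07.
- Age, assumed mean 30 and SD 9: √(1 + 11.11 × 20/19) = √12.70 = 3.56. Noncentrality is 2.95/3.56 = 0.83 and power about 0.12.

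Simulation with other assumed distributions agrees. With age uniform on 18 to 50, power is 0.11; adding IQ (mean 105, SD 12) gives 0.07; five covariates give 0.05. Type I error stays near 0.05, so the damage is lost power. Where the covariate also modifies the effect, the test is of a different quantity.

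**The case against.** A reader might infer that covariates invalidate both main treatment tests. The article does not support that.

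- **The confirmatory FC test is clean.** It is stated first, without PSG terms, and the PSG step follows it. The Abstract and Power Analyses both present the FC-sleep link as a correlation, so the likely intent is association. For a single PSG variable, regressing FC on sleep or sleep on FC gives the same t-test of the link. This stands. What remains is that the Analysis Plan words the step as a covariate-adjusted comparison of conditions, which is not what the other two places describe.
- **The sleep covariates are not named.** PSG Analysis does not say that IQ, age or any other trait enters, and several items in Table 1's block vary by visit. This also stands: use of fixed traits is a possibility that the article leaves open, not a stated choice.
- **The power collapse needs a particular implementation,** namely uncentred entry with condition interactions. With centring the loss is negligible. Such detail may sit in a fuller plan, so its absence here is not itself a fault.

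What survives is what the article does fix: a step worded as a PSG-adjusted treatment comparison, and a covariate-adjusted model as the confirmatory within-person sleep test, beside a covariate list that includes visit-1-only traits.

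**Conclusion.** The point holds in limited form and should be corrected. Taken literally, the PSG step is a post-treatment adjustment that could cut an assumed 0.66 SD contrast by 25% to 50% at a correlation of 0.5, or give 25% false rejection when only sleep responds. It does not touch the stated confirmatory FC test. In the sleep model, person-level covariates bring no protection against confounding. The cost runs from about 2 points of power (five covariates, centred) to near-total loss, 80% down to about 7 to 12% with one uncentred covariate. A reader might conclude that the sleep test is already ruined; the article does not show this, because it names neither the covariates nor how they enter. All sizes rest on assumed values for the effect, the correlation and the covariate distributions, since the article gives none.

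**What to change.** 1. State that the PSG-FC step is an association analysis only. Regress the within-person active-sham difference in one prespecified key PSG variable on the active-sham difference in FC change, with a period term. Draw no treatment-effect conclusion from an FC contrast adjusted for PSG.
2. Take the confirmatory sleep test from a paired or mixed model with condition and period. Period costs one df (19 to 18, power 0.799 to 0.797 at dz 0.66 if the residual SD is unchanged).
3. Drop person-level covariates from that test, or mean-centre them and use them only to examine effect modification.
4. Name any remaining covariates and restrict them to visit-specific values taken before stimulation.

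This changes wording and simplifies the models, on data already collected. The only downside is losing some planned adjustments. The article reports neuroimaging analysis as still under way, so the change should be dated and recorded before the contrasts are examined.
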